## Abstract

**Introduction:**

Liver transplantation remains the only curative option for end-stage liver disease, yet high waitlist mortality and organ scarcity continue to challenge the field. The randomised multicentre ExTra trial aims to decrease time-to-transplant by safely improving access to transplantation through viability assessment of otherwise discarded grafts with normothermic machine perfusion (NMP).

**Methods and analysis:**

The ExTra trial is a prospective, randomised, multicentre study conducted across German transplant centres. Participants listed for liver transplantation with a reMELD-Na-Score ≤21 (refitted MELD-Natrium Score) who are not eligible for Standard or Non-Standard Exceptions will be randomised for a 1-year intervention period into two groups: the experimental arm, in which they have—in addition to regular organ allocation—the extra option to receive a graft that was initially deemed non-transplantable based on clinical criteria, but meets specified quality criteria after at least 4 hours of NMP, and the control arm, which consists of conventional allocation procedures alone. The primary endpoint is time-to-transplant, defined as the period between randomisation and transplantation. Secondary outcomes include competing events (death, disease progression or recovery without transplantation), graft and patient survival, quality of life and cost-effectiveness. Additional analyses will assess early graft function, length of hospital stay, biliary complications and 1-year post-transplant outcomes. A centralised biobank will collect perfusate, tissue and blood samples for biomarker research. Safety will be monitored through quarterly reviews by a Data Safety Monitoring Board.

**Ethics and dissemination:**

The study protocol received approval from the Institutional Review Board of the Charité – Universitätsmedizin Berlin on 2 April 2025 (EA1/04/25). Participating study centres will need local Institutional Review Board approval prior to initiation. This study complies with Good Clinical Practice guidelines and all applicable national and local regulations. Results will be disseminated during international and national conference meetings and through publication in a peer-reviewed journal with open access.

**Trial registration number:**

NCT06874296.

STRENGTHS AND LIMITATIONS OF THIS STUDYProspective, randomised, multicentre study design evaluating back-to-base normothermic machine perfusion (NMP) for declined liver grafts.Predefined viability criteria, ensuring reproducible organ assessment and minimising intercentre variability.Comprehensive endpoint framework combining waitlist period, perioperative outcomes and graft and patient survival, enabling a clinically meaningful evaluation of NMP effectiveness in expanding the donor pool.Multicentre study design increases methodological robustness and reduces the risk of centre-specific biases, although practice differences in postoperative management may still influence outcome variability.Reliance on the real-world availability of declined donor grafts that fulfil predefined NMP viability criteria may impede reaching the planned number of primary endpoint events.

## Introduction

### Background and rationale

 Liver transplantation (LT) is the preferred treatment for patients with advanced liver cirrhosis, hepatocellular carcinoma within Milan criteria and severe metabolic or autoimmune liver disease.^1^ However, the number of patients on the liver transplant waiting list exceeds the number of available organs. In Germany, the success of LT has been undermined by a dramatic decline in organ donations over the past decade.^2
3^ In 2022, only 748 out of 1296 patients (58%) on the waiting list received a liver graft.^4^ The outcome for patients on the waiting list remains unsatisfactory: A study from Essen showed that the 12-month survival rate without transplantation was 46%, compared with 78% after a liver transplant.^5^ Comprehensive data from the Eurotransplant registry show that between 2006 and 2015, 32% of patients were removed from the waiting list because they became too ill to receive a graft or died while waiting.^6^ This problem particularly affects patients with a lab MELD ≤25 (Model for End-Stage Liver Disease) who are not eligible for Standard or Non-Standard Exception criteria. Patients whose disease severity is not adequately reflected by lab MELD can, at the initiative of the transplant centre, be requested for an exceptional MELD; disease and country-specific rules apply.^7^ These patients wait significantly longer for a graft (2022: 112 vs 54 days, p<0.001) and have a significantly lower 12-month transplantation rate (44% vs 70%, p<0.001, unpublished data from Eurotransplant) compared with the general population of listed patients. The imbalance between supply and demand is further exacerbated by the fact that about 24% of all liver grafts offered for transplantation in Germany are declined due to the donor’s age or overall morbidity.^8^ This issue exists worldwide, with discard rates in the USA being similarly high (13%).^9^

The liver allocation process in Germany is strictly regulated and managed by Eurotransplant, in cooperation with the German organ procurement organisation ‘Deutsche Stiftung Organtransplantation’ (DSO, German Organ Transplantation Foundation). Each organ is allocated according to a specific algorithm. The decision to accept or reject a liver graft for a recipient is based on appropriately matching the donor’s clinical data with that of a potential recipient, as well as logistical considerations. To address the current organ shortage, liver grafts from donors with extended criteria (ECD) are increasingly used for transplantation.^10^ However, up to 24% of all liver grafts offered for transplantation are declined, mainly due to the donor’s age, macrosteatosis or long cold ischaemia time, as these factors are associated with an increased risk of graft dysfunction, graft failure and death, particularly in recipients with a high MELD score.^8
11–13^ The decision-making process is primarily based on the subjective expertise of the accepting transplant surgeon, supported by scores that consider both donor and recipient factors.^14
15^ Objective tools for assessing graft function are not routinely used in clinical practice for conventional static cold storage. For hypothermic oxygenated liver machine perfusion (HOPE), there are reports for measuring flavin mononucleotide and nicotinamide adenine dinucleotide to assess graft quality, although there is still ongoing need for prospective trials to internationally validate these criteria.^16
17^ Pilot studies have shown that normothermic machine perfusion (NMP) enables the assessment of organs clinically deemed unsuitable for transplantation using viability criteria such as lactate clearance or bile production.^18
19^

Transplantation of initially declined liver grafts following quality assessment by NMP has been investigated in eight non-randomised, single-centre clinical studies in the UK, the Netherlands, Australia, Italy, and the USA.^20–26^ The commercially available OrganOx Metra (OrganOx, Oxford, UK), the Liver Assist device (XVIVO B.V., Groningen, Netherlands), the Aferetica PerLife (Aferetica s.r.l., Bologna, Italy) and a non-commercial device developed in Cleveland were used in these studies. The OrganOx Metra and the institutionally developed device were used for pure end-ischaemic perfusion,^20
21
23
24
26^ while the protocol established in Groningen for the Liver Assist device consisted of 1 hour of HOPE, followed by controlled oxygenated rewarming (COR) and 2.5 hours of NMP for quality assessment.^22
25^ This protocol was also used in a modified form (90 min of COR and dual HOPE) in one study that employed both the Liver Assist and Aferetica PerLife devices.^27^

The ExTra trial will randomise patients on the waiting list to demonstrate that declined liver grafts, which meet predefined quality criteria after at least 4 hours of NMP, can be used to reduce the waiting time for LT in patients with a low MELD score who are not eligible for Standard or Non-Standard Exceptions. This is of clinical relevance given the increasing number of livers declined for transplantation in Germany, despite new technologies enabling quality assessment of these potentially transplantable organs. The utilisation rate of grafts, safety, cost-effectiveness and the effect on the waiting list practice will be evaluated as secondary endpoints. The results of this study could therefore change clinical practice in Germany and help address the medical-social dilemma of organ shortages in LT by integrating graft quality assessment through NMP into clinical practice. This could enable the acceptance of livers that are currently declined, which would certainly increase organ utilisation in Germany. To further leverage the impact of this clinical study, a translational companion study will be conducted to identify novel biomarkers for assessing and predicting graft quality in NMP.

### Objective

The objective of the ExTra trial is to demonstrate that the waiting time for LT in patients with a reMELD-Na score ≤21 (corresponds to labMELD ≤25), who are not eligible for Standard or Non-Standard Exception criteria, can be significantly reduced by using liver grafts that were initially deemed non-transplantable based on clinical criteria but meet predefined quality criteria after at least 4 hours of end-ischaemic NMP, compared with patients who are not offered this option. By analysing this procedure across participating study centres, we aim to safely transform organ acceptance practices in Germany, provided the results are successful.

## Methods and analysis

### Study design and timeline

This is an investigator-initiated prospective, multicentre, randomised, open-label, two-arm clinical study. In total 186 patients will be randomised 1:1 to the experimental or control arm (figure 1). LT in the context of regular organ allocation can be performed in both arms according to the centre’s decision, that is, using static cold storage, hypothermic or NMP for organ preservation. Quality assessment of grafts judged clinically unacceptable by NMP is reserved for the experimental arm.

**Figure 1 F1:**
[figure not shown]
Visual presentation of patient timeline after randomisation in the ExTra trial. LT, liver transplantation; NMP, normothermic machine perfusion; reMELD-Na, refitted MELD-Natrium Score.

The proposed study duration is 66 months (1 June 2025–31 December 2030). The study started recruiting on 2 June 2025, with an anticipated recruitment period of 36 months, concluding on 31 May 2028. Each participant will be enrolled in the study for a maximum duration of 24 months, comprising an intervention phase of up to 12 months, followed by a 12-month structured follow-up period after transplantation (online supplemental table 1). The final participant follow-up is expected to be completed by 31 May 2030, after which the study will proceed with data analysis and dissemination activities. The study is scheduled to conclude by 31 December 2030.

### Eligibility criteria

All patients with a reMELD-Na ≤21 without eligibility for Standard or Non-Standard Exceptions, who are listed in the status transplantable for LT, and medically suitable and informed for transplantation with so-called marginal organs from donors, who meet extended donor criteria, will be recruited for the ExTra trial at the respective study centres.

#### Inclusion criteria

Before inclusion in the study, each patient is informed by the local study physician in charge about the nature, objectives, expected benefits and possible risks of the study, both orally and in writing. Patients are included while active on the waitlist. The duration of waitlist time before study inclusion is included in the randomisation stratification. Potential participants must demonstrate the capacity to (1) understand the study information, (2) retain the information, (3) weigh the risks and benefits and (4) communicate a clear decision. Only individuals who meet all four criteria are invited to participate. The decision is made by the treating physician.

The inclusion criteria are:

Able to consent.≥18 years old.Listed as status ‘transplantable’ by the transplant conference of the study centre for LT, according to the guidelines of the German Medical Association valid at the time of inclusion.reMELD-Na ≤21, not eligible for Standard or Non-Standard Exceptions.Standard and Non-Standard Exceptions are defined in the Eurotransplant liver allocation manual.Medically suitable and informed for transplantation with an organ that fulfils extended donor criteria (Eurotransplant ECD criteria).Patient information and written consent to participate in the ExTra trialIf the patient can give consent but is unable to sign personally, a witness must confirm the oral explanation by signing.No participation in another interventional study during participation.

#### Exclusion criteria

Listed for retransplantation.High-urgency listing.Listed for combined organ transplantation.Pregnancy.

### Recruitment

The primary recruitment measure should be a personal discussion as part of the information on LT during consultation hours. For this purpose, the respective doctors providing information and the transplant office in the recruiting centres will be informed and sensitised. In addition, information flyers will be made available in the respective transplant outpatient clinics so that potential study participants can inform themselves independently. All patients who present themselves personally on the waiting list as part of routine management (eg, laboratory check for the reMELD-Na score) and fulfil the inclusion criteria should also be contacted personally.

### Randomisation

Patients are randomised as block randomisation in a 1:1 ratio. Randomisation is centrally managed through the electronic case report form (eCRF). This means that patients will be evenly distributed between the two study arms (control group with standard allocation and experimental group with the ExTra option).

To ensure an even distribution of key clinical characteristics across both treatment arms, the randomisation will be stratified according to the following prognostic variables:

reMELD-Na-Score at the time of randomisation (<13 or ≥13),Waiting time prior to randomisation (0–6 months or >6 months).

### Interventions

#### Experimental arm

The experimental intervention, that is, the ExTra option, will be offered for a period of 12 months from randomisation, due to the expected medical deterioration of patients on the waiting list. In the experimental arm, treatment consists of either:

ExTra-LT: receiving a liver transplant with a graft that has been declined by all German transplant centres but meets established objective quality criteria during NMP.LT: receiving a liver transplant via the regular liver allocation process when a graft becomes available, whichever occurs first.

Graft procurement and liver allocation are handled by Eurotransplant, in cooperation with the German organ procurement organisation DSO. To the best of our knowledge, organs are procured ethically and are not sourced from executed prisoners or prisoners of conscience or other vulnerable groups. The study team is not involved in the care of organ donors prior to organ donation. In Germany, post-mortem organ donation is regulated by the German Transplantation Act: the DSO coordinates the donation process on behalf of the donor hospitals, including donor identification and evaluation, verification of consent documentation and the logistical coordination of donor management, organ procurement and transport, whereas Eurotransplant is responsible for allocating the procured organs across its member countries according to defined, MELD-based allocation rules for liver grafts.

#### Quality assessment

Declined liver grafts considered for quality assessment must not have macrovesicular steatosis >60%, fibrosis grade >F3 or cirrhosis (based on histopathologic quick section analysis, if requested by the responsible transplant surgeon after macroscopic examination) and have a graft weight between 1 and 2.5 kg. Moreover, grafts must be connectable in terms of vascular anatomy. The goal is to maintain a dropout rate of no more than 50% for grafts that either fail quality assessment via NMP or cannot be safely transplanted despite undergoing NMP quality assessment. Additionally, the organ must not yet have been treated using a dynamic preservation procedure (HOPE or NMP).

As part of the ExTra LT quality assessment, the liver is removed from the cold preservation solution in the transplant centre in an end-ischaemic ‘back-to-base’ approach, prepared, cannulated and connected to the liver perfusion machine according to the respective manufacturer’s specifications. The decision to use or reject a graft after quality assessment by NMP (ie, start of recipient hepatectomy) is made at least 4 hours after the start of perfusion by the transplant surgeon, based on:

Lactate levels <2.5 mmol/L.And two or more of the following:Evidence of bile production.Maintenance of a perfusate pH >7.30 (without correction for at least 1 hour).Glucose metabolism (falling perfusate glucose value with consistent downward trend).Maintenance of stable arterial and portal venous flows (if using OrganOx Metra: 150 and 500 mL/min, respectively).Homogeneous perfusion with soft consistency of the parenchyma.

If the liver fulfils the above criteria after 4 hours of perfusion and is assessed as safely transplantable based on the assessment of the transplant surgeon in charge, the recipient is then initiated for surgery and the liver is transplanted. The quality assessment is device-independent (currently usable: XVIVO LiverAssist, OrganOx Metra or Aferetica PerLife). Additionally, a combination of HOPE and COR prior to the 4 hours of quality assessment with NMP is possible.

If patients are not transplanted within 12 months, they continue to be regularly listed on the waiting list without the possibility for an ExTra-LT and are censored.

#### Control arm

In the control arm, patients receive a liver graft following the regular allocation procedure. Both patients who receive an ExTra LT or a liver graft after standard allocation are followed up in hospital and after discharge at 3 months, 6 months and 12 months.

#### Criteria for discontinuing or modifying allocated interventions

Participation in the ExTra trial is voluntary, and participants have the right to withdraw from the study at any time, at their own request and without giving reasons. The following events can be considered as discontinuation criteria:

Personal wish of the patient.Pregnancy.Serious complications.Significant protocol violations.Loss of contact, change of location or change of treating physician.

In addition, there are specific criteria that can lead to exclusion:

Withdrawal of consent to accept livers with expanded donor criteria.Organ failure requiring combined organ listing.Disease progression while listed as non-transplantable: If a patient is deemed non-transplantable due to an infection or other event and the reMELD-Na is >21, patients are not directly excluded. The period of non-transplantable status is documented, and the reMELD-Na score reevaluated once the patient reaches a transplantable state. Only if the patient is listed as status as transplantable and the reMELD-Na remains >21 points, patients can no longer participate in the study. Survival data is censored up until this point.

#### Strategies to improve adherence to interventions

Patients are managed by the respective study centre as part of the waiting list management for LT. This includes, for example, regular blood samples for updating the reMELD-Na score to determine urgency. As part of the study, compliance is expected to be similar to the waiting list for LT. Ensuring compliance is the responsibility of the respective study centres or the transplant programme.

### Outcomes

#### Primary endpoint

The primary endpoint ‘time-to-transplant’ is defined as the time between randomisation and transplantation. Results will be evaluated on the intention-to-treat cohort, the hazards between experimental arm and control arm are compared using cause-specific Cox proportional hazards models.

#### Secondary endpoints

The secondary endpoints include, among others, competing events (death, disease progression, recovery) and are also evaluated on the intention-to-treat cohort. Again, the time from randomisation until the occurrence of the event is examined. For death (corresponds to waiting list mortality) and the composite of disease progression and recovery, cause-specific Cox proportional hazards models are calculated. The same variables as for the primary endpoint are used for adjustment (reMELD-Na score and waiting time), in addition to perfusion device used (OrganOx Metra, LiverAssist or Aferetica PerLife), study centre, age and sex. Furthermore, of particular interest are the number of patients still listed for transplantation after 12 months, the overall patient survival (from randomisation to death), the quality of life (EuroQol-5 Dimension, 5-Level questionnaire - EQ-5D-5L), the graft utilisation rate (used organs/offered organs for patients on the waiting list) as well as transplantation-associated costs.

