### Sample size

The primary statistical objective is to show that the cause-specific HR for the transplant risk between the two randomised groups is not equal to 1. The assumptions for the data-generating process are based on data from Eurotransplant in 2022: Within 12 months, 43.6% of patients with a MELD ≤25 (corresponds to reMELD-Na ≤21) who were not eligible for Standard or Non-Standard Exception were transplanted, 19.1% had a competing event (death, progression or recovery) and 37.2% remained on the waiting list and were censored in this study.

As a treatment effect, an increase in the transplantation rate of 20% to 63.6% was assumed, while the risk of the competing event remains unchanged. A 20% increase in the transplantation rate through the ExTra option is realistic, as 385 LTs were performed in Germany in 2022 in patients with MELD ≤25 without standard/non-standard exception MELD criteria, while 133 of 217 declined grafts would have been potentially acceptable after a quality assessment using NMP, representing approximately 20% additional grafts in the study population based on an estimated 50% acceptance rate following NMP.

Assuming exponential distributions for time to transplant and time to competing event, the data were simulated to fit this pattern. The parameter of the exponential distribution for time to transplant (in months) was 0.057 for the control group and 0.104 for the intervention group. The parameter for the competing risk was 0.0251 for both groups. A Cox proportional hazards model was used to estimate the transplant HR between the ExTra LT group and the control group.

Based on 1 000 000 simulations, a sample size of N=83 per group was calculated for a two-sided type I error of 0.05 and a power of 0.8. Considering a dropout rate of 10%, a total of 93 patients will be recruited per group. A median of 36 transplantations is expected in the control arm. It is expected that 4–29 additional transplantations (median: 17) will be performed in the experimental arm.

This number of cases can probably be reached with a recruitment period of 36 months. A 12-month intervention phase is planned, followed by a 12-month follow-up phase. The study will thus end when all 83 patients in each treatment group have completed the 12-month follow-up after randomisation/transplantation.

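### The secondary Cox endpoint that pools disease progression with recovery has no direction of benefit, so its hazard ratio cannot be read as gain or harm

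*Protocol article*

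**What the plan says.** The Secondary endpoints section of the protocol article first names three event types: "The secondary endpoints include, among others, competing events (death, disease progression, recovery) and are also evaluated on the intention-to-treat cohort". It then states cause-specific Cox models for two outcomes: "For death (corresponds to waiting list mortality) and the composite of disease progression and recovery". Death therefore has its own model, while progression and recovery share one. The section gives no direction of benefit for the shared model, no reason for pooling, and no model for either component alone.

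Elsewhere the article shows that the two components point in opposite directions. The abstract describes the events as "competing events (death, disease progression or recovery without transplantation", so recovery means no longer needing a graft. Under the criteria for discontinuing or modifying allocated interventions, the disease-progression item concerns patients whose score has worsened: "Only if the patient is listed as status as transplantable and the reMELD-Na remains >21 points, patients can no longer participate in the study".

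The Sample size section gives one figure for all three types together: "19.1% had a competing event (death, progression or recovery", with no split.

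**The concern.** A composite hazard ratio can be interpreted only if its components point the same way. Here they do not. A value below 1 may reflect less deterioration, which is good, or less recovery, which is bad. A value near 1 may reflect no effect on either component or two effects that offset each other.

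Pooling is harmless in the primary model. There every competing event is censored at its occurrence, and its type does not enter the transplant hazard ratio. The difficulty arises because the pooled category is also a secondary outcome with its own treatment hazard ratio. A reader of the trial report would want to know whether the ExTra option changed the rate of deterioration on the list, and the specified model cannot say.

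**Working it through.** **Step 1: reproduce the plan's figures.** Inputs from the Sample size section are monthly exponential rates for transplant of 0.057 (control) and 0.104 (experimental), a competing-event rate of 0.0251 in both groups, 12 months, and 83 per group. With transplant rate l and competing rate k, the 12-month cumulative incidence of a competing event is k/(l+k) × (1 − exp(−12(l+k))). For transplant, l replaces k in the numerator.

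- Control: l+k = 0.0821 and 1 − exp(−0.985) = 0.627. Transplanted 43.5%, competing event 19.2%, still waiting 37.3% (stated: 43.6%, 19.1%, 37.2%).
- Experimental: l+k = 0.1291 and 1 − exp(−1.549) = 0.788. Transplanted 63.4% (stated: 63.6%), competing event 15.3%.

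The planning model reproduces.

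**Step 2: expected competing events.** 83 × 0.1916 = 15.9 in control and 83 × 0.1531 = 12.7 in the experimental arm. That is 28.6 in all, or about 29, with deaths included. The article does not say how many are progression or recovery. If 30% to 70% are (assumed range), the composite has 0.30 × 28.6 = 8.6 to 0.70 × 28.6 = 20.0 events.

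**Step 3: what the composite hazard ratio measures.** Let f be the share of progression in the control-arm composite hazard. With constant hazards,

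composite HR = f × HR(progression) + (1 − f) × HR(recovery).

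The article gives neither f nor the component hazard ratios, so all values below are assumptions. The last column is (1 − 0.5f)/(1 − f).

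| f | Favourable on both (0.5 progression, 1.5 recovery) | Unfavourable on both (1.5 progression, 0.5 recovery) | Recovery HR that exactly offsets a progression HR of 0.5 |
|---|---|---|---|
| 0.25 | 1.25 | 0.75 | 1.17 |
| 0.50 | 1.00 | 1.00 | 1.50 |
| 0.75 | 0.75 | 1.25 | 2.50 |
| 0.90 | 0.60 | 1.40 | 5.50 |

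Three results follow.

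- The same pair of favourable effects falls on either side of 1 depending on f.
- At f = 0.50, favourable on both and unfavourable on both each give 1.00.
- A composite of 0.75 arises from favourable effects at f = 0.75 and from unfavourable effects at f = 0.25. At f = 0.50 it also arises from halving progression alone (0.5 × 0.5 + 0.5 × 1 = 0.75) or from halving recovery alone (0.5 × 1 + 0.5 × 0.5 = 0.75).

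The last column shows the limit of the concern. If progression dominates, complete cancellation needs an implausibly large effect on recovery.

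**Step 4: does pooling buy precision?** Approximate power at two-sided 0.05 with d events and equal allocation is Φ(½√d × |ln HR| − 1.96). For a composite HR of 0.5 this is about 17% at 8.6 events and 34% at 20. For 0.75 it is about 6% and 9%. Pooling does not turn this into a confirmatory analysis.

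**The case against.** The strongest defence is that a competing-risks report should account for every way of leaving the risk set, and that a residual category of exits other than death is a normal way to do this with few events. The model adjusts for reMELD-Na, waiting time, device, centre, age and sex, and separate models would have fewer events still. That explains the pooling and justifies it as bookkeeping. It does not give the pooled hazard ratio a meaning as an endpoint.

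A second defence is that the section lists the three event types individually, and an analysis plan that is not shown may tabulate them. That may be so, and the absence of such tables from an article is no fault. The point rests on the composite that the article does state, which would lack a direction whatever is added beside it.

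A third is that the Secondary endpoints section does not define disease progression, and that the exit described under the discontinuation criteria concerns a patient who is still transplantable under MELD-based allocation. Equating the two is an inference, and this exit is not comparable to death. It is nevertheless a worsening, and recovery is its opposite.

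Stronger readings that a reader might infer are not supported:

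- *Cancellation is to be expected because ExTra grafts would go first to sicker candidates.* The article does not say how these grafts are distributed within the experimental arm. Such a pattern would also be selection among those still waiting, which separate models would not remove. The Sample size section assumes that "an increase in the transplantation rate of 20% to 63.6% was assumed, while the risk of the competing event remains unchanged". That is a planning assumption and does not settle the matter either way.
- *The information would be lost for good.* The event types are named separately, so they could be tabulated if exit type is recorded. The article does not describe how it is recorded.
- *The trial's main conclusion or safety oversight is compromised.* The primary model censors these events, death has its own model, overall survival and the number still listed at 12 months are further secondary endpoints, and the safety board looks at 3-month graft and patient survival.

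**Conclusion.** The point holds for one secondary analysis. As specified, the pooled hazard ratio for progression and recovery cannot be read as benefit or harm. This follows from the opposite direction of the components and needs no numerical assumption. The possible size of an offset cannot be computed from the article. The range of 0.60 to 1.25 for effects favourable on both components rests on assumed component hazard ratios of 0.5 and 1.5, constant hazards, and an assumed progression share of 25% to 90%. It shows what can happen, not what is likely. The count of about 29 competing events rests on the plan's own rates and 83 per arm. The matter is worth correcting before results are seen, but it does not touch the primary endpoint, the sample size or the power calculation.

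**What to change.** In the Secondary endpoints section, replace the composite with separate analyses of disease progression and of recovery. Each should have a cause-specific hazard ratio and a cumulative incidence per arm, labelled descriptive if events are few. If pooling is wanted because events are sparse, pool only outcomes of the same direction, for example death or progression, and show the components beside the pooled result. That alternative is optional. It is close to the outcome used in the Background, where 32% of patients were removed because they died or became too ill, but it mixes events of unequal gravity.

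The cost is a change of wording and a few extra estimates, provided that the case report form codes the type of exit; the article does not say so, and this should be confirmed. The downside is that each component will have few events and wide intervals, probably too few for the full covariate list. No change to the primary analysis or the number of patients is needed.
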